#### Statistical Analysis

2.7.2

Statistical analyses will be performed using the biometry unit of the Center of Clinical Investigation of Rennes. Interim analyses will not be performed. Patients randomized and undergoing ablation will be analyzed on a “modified intention‐to‐treat” basis. Only patients with a persistent left intraventricular thrombus that definitely contraindicates ablation will be excluded. The expected exclusion rate is very low ( < 3%) and exclusion is not expected to be dependent on the allocated treatment arm. The clinicopathological criteria at inclusion will be described for all patients as well as for each of the two study arms: (i) qualitative variables will be presented as counts and percentages, and (ii) quantitative variables will be presented as means, standard deviations, quartiles, minimums, and maximums. The normality of the distribution of quantitative variables will also be assessed graphically and/or using the Shapiro‐Wilk test, if necessary. The primary endpoint is a censored variable; therefore, both groups will be compared using the log‐rank test. Secondary endpoints will be analyzed according to the type of variable: (i) quantitative variables will be analyzed using the Student's *t*‐test or the Mann–Whitney test if necessary; (ii) qualitative variables will be analyzed using the Chi‐square test or Fisher's exact test if necessary; (iii) censored variables will be analyzed using the Log‐rank test.

Adjustments may be made in cases with heterogeneity at inclusion. The conditions for applying these tests or models will be verified before their implementation. All the tests will be conducted at a significance level of 5%.

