### Patient Population

2.2

Participation in the study may be offered to ICM patients requiring VT radiofrequency ablation, either during consultation (outpatient) or during hospitalization (for inpatients requiring urgent intervention). Participation in the study will be proposed and explained to the patient along with the provision of an information letter. Signed informed consent will be obtained before patients are randomized. Antithrombotic treatment will be adapted according to the randomization group. Randomization will be centralized through the Ennov software (Ennov Clinical, Groupe Ennov, Paris, France), generating blocks of variable size to ensure the unpredictability of treatment allocation. The block sizes and order of treatment within each block will be randomly generated. Randomization will be stratified by center.

Patients must meet the following criteria to be eligible for the study: (i) patients aged > 18 years, (ii) requiring first‐time radiofrequency ablation for VT associated with ICM, (iii) implanted with an ICD and monitored remotely through telemonitoring, (iv) for women of childbearing age, use of effective contraception until hospital discharge, (v) provision of written informed consent, and (vi) affiliated with a health insurance system or benefiting from such coverage.

Patients meeting any of the following criteria will be excluded from the study: (i) history of cardiac surgery compromising epicardial access (such as coronary artery bypass grafting, valve replacement, or other surgeries that may have caused pericardial adhesions), (ii) presence of a left ventricular thrombus detected on pre‐procedure imaging, (iii) use of anticoagulant therapy that cannot be temporarily discontinued, (iv) use of dual antiplatelet therapy that cannot be temporarily replaced by single antiplatelet therapy, (v) history of pericarditis, (vi) history of thoracic radiotherapy, (vii) contraindication to general anesthesia, (viii) pregnant or breastfeeding women, (ix) history of type 2 heparin‐induced thrombocytopenia (as heparin injection is required during the procedure), and (x) adults under legal protection (e.g., guardianship, curatorship), deprivation of liberty, or inability to provide informed consent.

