#### Sample Size Estimation

2.7.1

In two meta‐analyses investigating ICM patients outcomes after endo‐epicardial ablation, the risk of ventricular arrhythmia recurrence at 2 years was 50% in the ‘endocardial‐only’ group and 26% in the ‘endo‐epicardial’ group (HR = 0.43) [20, 21]. To demonstrate this difference, it is necessary to observe 59 events to ensure 90% power with a two‐sided α risk of 5%. To observe a minimum of 59 events required for analysis, we planned to evaluate 150 patients followed for a period of at least 2 years. After the 2‐year follow‐up, patients will no longer be monitored as part of the study, but the ICDs will be remotely interrogated via telemonitoring for patients with no recurrence until (i) arrhythmia recurrence or at the latest (ii) the date of the last visit of the last patient included.

Of note, the sample size estimation is based on treatment effect derived from a prior meta‐analysis of observational studies. However, we acknowledge that the endocardial ablation strategies varied significantly across the included studies, ranging from targeted ablation of clinical/induced VT to complete scar homogenization. This heterogeneity may have influenced the estimated benefit of a combined endo‐epicardial approach and represents a limitation of the current power calculation.

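### Covariate adjustment is left to depend on baseline imbalance seen after randomisation, with no criterion, covariate list or stated role; fix the adjustment in advance and say how centre is handled

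*Protocol article*

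**What the plan says.** All references are to the protocol article.

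- **Primary test (2.7.2, Statistical Analysis):** "The primary endpoint is a censored variable; therefore, both groups will be compared using the" log-rank test. No centre term, stratification or covariate is named.
- **Adjustment (2.7.2, closing paragraph):** "Adjustments may be made in cases with heterogeneity at inclusion". The text does not say what counts as heterogeneity, which variables are considered, which model is used, or whether the adjusted result supports or replaces the log-rank.
- **Level:** "All the tests will be conducted at a significance level of 5"% (2.7.2), with a "two‐sided α risk of 5"% in the sample size section (2.7.1).
- **Randomisation (2.2, Patient Population):** "Randomization will be stratified by center", in blocks of variable size. Centre is the only stratification factor named. Section 2.1 states 13 centres but lists 12.
- **Size (2.7.1):** "it is necessary to observe 59 events to ensure 90% power"; "we planned to evaluate 150 patients followed for a period of at least 2 years". The assumed HR is 0.43.
- **Baseline data (Table 1):** medications taken are recorded at the inclusion visit.

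**The concern.** Any difference between randomised arms at baseline is chance. A rule that adjusts when such a difference is noticed has two costs.

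First, it brings adjustment into play according to observed imbalance. The gain in power from adjustment comes mainly from how strongly a covariate predicts recurrence, and that gain is available when the covariate is balanced too. A trigger throws most of it away.

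Second, the permissive wording fixes neither trigger nor model. In an open-label trial, someone who has seen the data could report whichever of several results is more favourable, and the nominal 5% level would then not be protected. Even if nobody does so, the published text could not rebut the suspicion.

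Centre is a related but lesser matter. Blocking within centre makes the arms more alike than simple randomisation would. If centres differ in recurrence, a log-rank that ignores centre uses too large a variance and becomes conservative.

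**Working it through.** **1. The plan's own figure.** Schoenfeld's formula, 1:1 allocation, two-sided 5%, 90% power, HR 0.43:

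events = 4(z₀.₉₇₅ + z₀.₉₀)² / (ln HR)² = 4(1.960 + 1.282)² / (ln 0.43)² = 42.03 / 0.7123 = 59.0.

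The stated 59 reproduces, and power at 59 events is 90.0%. This formula describes a log-rank with no centre or covariate term. The event count is not in dispute.

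**2. How often chance imbalance would trigger adjustment.** The plan gives no number of covariates. Assuming five independent ones, each tested at 5%: 1 − 0.95⁵ = 22.6%. In simulation, 22–25% of trials were triggered.

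**3. What the rule does to power and type I error.** From the plan: 150 patients, 1:1, 50% control recurrence at 24 months, HR 0.43. Assumed: exponential times, all patients censored at 24 months, five standard normal covariates of which two are prognostic, with log-HR 0.3 or 0.5 per SD (HR 1.35 or 1.65). There were 3,000 runs per scenario, so the Monte Carlo standard error is about 0.6 point for power and 0.4 for type I error. Expected events at 24 months are 75 × 0.50 + 75 × 0.26 = 57. Follow-up beyond 24 months is not modelled, so the comparisons matter more than the absolute power.

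| Cox analysis | Power, HR 0.43 (log-HR 0.3 / 0.5) | Type I error (0.3 / 0.5) |
|---|---|---|
| Never adjusted | 85.3% / 81.8% | 4.8% / 5.2% |
| Adjusted only if a baseline test is significant | 85.3% / 82.3% | 4.7% / 4.7% |
| Always adjusted for the two prognostic covariates | 88.4% / 89.4% | 5.3% / 5.4% |
| Most favourable of unadjusted, five single-covariate and full models | not a valid comparison | 8.2% / 10.0% |

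The trigger gains 0.0 and 0.5 point over never adjusting. Fixed adjustment gains 88.4 − 85.3 = 3.1 and 89.4 − 82.3 = 7.1 points over the trigger. At HR 0.55 the same comparison is 60.8% to 65.0% and 55.7% to 65.8%.

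A separate simulation (1,200 runs, two binary covariates with HR 2.0–2.5 each) points the same way: 89.4% and 87.5% when triggered, 91.7% and 92.9% when always adjusted.

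**4. Centre.** Average size is 150/13 = 11.5 to 150/12 = 12.5 patients, and 59/13 = 4.5 to 59/12 = 4.9 events, per centre. Assumed: blocks of 2 and 4, and log-normal centre hazards with SD from 0 to 1.0, since the article gives no between-centre figure. Results for 13 centres (equal / unequal sizes), 3,000 runs:

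| SD of centre log-hazard | Power, plain log-rank | Power, centre-stratified log-rank | Type I error, plain |
|---|---|---|---|
| 0 | 88.2 / 89.0% | 86.3 / 87.9% | 4.7 / 5.7% |
| 0.3 | 86.6 / 87.0% | 86.4 / 86.6% | 5.5 / 5.1% |
| 0.5 | 86.9 / 87.2% | 88.0 / 88.1% | 4.1 / 3.7% |
| 0.8 | 82.7 / 82.4% | 88.1 / 87.5% | 2.5 / 3.4% |
| 1.0 | 78.1 / 78.2% | 88.1 / 87.5% | 1.9 / 2.1% |

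The stratified test's type I error stayed between 4.7% and 6.0%. An SD of 0.8 is large: centres one SD above and one SD below the mean differ by exp(1.6), about five-fold, in hazard.

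A Cox model with a random centre effect was compared with the plain log-rank in 600 runs with longer assumed follow-up and 8% yearly loss. Power was 94.7% for both at SD 0, 92.8% against 90.5% at SD 0.5, and 93.7% against 88.2% at SD 0.8. The standard error is about 1.2 points, so the middle difference is not firm.

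**The case against.** **The adjustment sentence may be harmless.** It is permissive, sits in a separate paragraph after the secondary endpoints, and does not say that an adjusted result displaces the log-rank, which is named without condition. Applied mechanically, the trigger leaves type I error at 4.7%. This stands: a reader might infer that the plan inflates its error rate to 8–10%, but that figure needs an analyst free to pick the best of several models. The text permits that reading; it does not prescribe it. The answer to an ambiguous sentence is still to settle it, and the loss of power arises even on the harmless reading.

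**Details belong in the analysis plan.** A covariate list and a centre term are commonly left there, and that plan is not shown. This disposes of any complaint about silence. It does not dispose of the sentence itself, which commits in print to adjustment driven by the data.

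**The centre point can be overstated.** A reader might infer that the primary test is definitely unstratified and therefore wastes power. The article never says unstratified, and gives no figure for centre differences. Sections 2.3.2 to 2.3.4 set a common substrate strategy, stimulation protocol and ICD recommendations, which limits some variation, although ventricular access follows local practice and antiarrhythmic drug management is left to the treating physician. With no centre effect the fully stratified log-rank loses 1 to 2 points in the table above. Where centres differ, the plain test errs only on the conservative side. A plain log-rank can therefore be defended; the plan should give the reason.

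**Conclusion.** The concern holds for the conditional adjustment. As worded, the rule lets chance imbalance bring adjustment into play, recovers almost none of the power of fixed adjustment (about 3 to 7 points lower for covariates of the assumed strength), and protects the 5% level only if trigger and model are fixed and followed. The size rests on assumptions the article does not supply: five candidate covariates, two of them truly prognostic, and a fixed list that picks exactly those two. Weaker or badly chosen covariates would shrink the gain.

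On centre, only a conditional statement is supported. The plain log-rank costs nothing at SD 0 and about 5 points at SD 0.8. At SD 0.5 the stratified test is better by about 1 point with 13 centres, and by 87.3 − 85.5 = 1.8 and 87.0 − 85.6 = 1.4 points with 12. The documents do not support a claim that the plan's type I error is inflated by ignoring centre, that its 59 events are wrong, or that one particular centre model is obligatory.

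This is an inexpensive improvement to the stated method, not a flaw that invalidates the primary comparison.

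**What to change.** 1. Delete the conditional-adjustment sentence.
2. Fix before database lock, without sight of outcomes by arm, a short list of prognostic covariates already recorded at inclusion. Baseline antiarrhythmic drug use is an example, since Table 1 records medications at that visit. Adjust for the list in a Cox model in every case, whatever the observed balance.
3. State in advance which of the log-rank and the adjusted model is primary; the other is a sensitivity analysis.
4. Account for centre in the model, for example by a random centre effect, or give the reason for a plain log-rank. Stratifying the log-rank on all 12–13 small centres is not free when centres do not differ. Reconcile the 13 centres stated with the 12 listed, so that the number of strata is clear.

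**Cost.** No patients, visits or new data. If the log-rank stays primary, this is analysis wording only. If the adjusted model becomes primary, the protocol's named primary test changes after recruitment has begun, and the change should be dated and documented; the article plans no interim analysis. The adjusted analysis is slightly more complex, and its hazard ratio is conditional on the covariates rather than marginal, which the report should say.

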### Limitations

2.8

An inherent limitation of this study is the exclusion of patients with prior coronary artery bypass grafting (CABG), a significant subgroup of patients with ischemic cardiomyopathy undergoing catheter ablation. While the inclusion of this group would introduce complexities, particularly in relation to epicardial access, we intentionally excluded these patients to maintain study feasibility and safety. As a result, the findings of this study may not be directly applicable to this subgroup, and further studies specifically focused on patients with prior CABG will be necessary to assess the optimal ablation strategy in this population.

This study exclusively utilizes radiofrequency ablation, and alternative energy sources such as pulsed field ablation (PFA) or large‐footprint radiofrequency catheters are not included. While these technologies are emerging, they are not yet widely implemented for ventricular tachycardia ablation. Given that patient enrollment is already well underway, we anticipate completing the study before the widespread adoption of PFA for ventricular applications. However, the potential future impact of these evolving technologies on VT ablation strategies should be considered when interpreting the generalizability of our results.

## Discussion

3

Since its first description in 1996 by Sosa et al. [10] epicardial ablation has been increasingly used for catheter ablation of VT. Since then, some cardiomyopathies have been described as having nearly exclusively an epicardial substrate, like Chagas cardiomyopathies or myocarditis, warranting a first‐line epicardial procedure. Conversely, the high success rate of surgical subendocardial resection, as of catheter ablation in patients with ICM [22] has paved the way for a sole endocardial procedure as first line therapy for such patients. However, despite major technological improvements in mapping catheters, ablation tools, and 3D mapping systems, and despite a relatively high acute success rate, many ICM patients will experience a VT recurrence over follow‐up [5, 6, 7, 8, 23]. Many reasons may explain recurrences, such as incomplete endocardial ablation, substrate remodeling [24, 25], or the presence of a hidden substrate in the epicardial face of the ventricle, or buried in the mid‐myocardium. Tung et al elegantly demonstrated that the epicardium was a functional component of the VT circuit in the majority of post‐infarct arrhythmias [9]. Indeed, only 7% of ICM VTs exhibited propagation with complete reentry confined to the endocardium or the epicardium, while the vast majority (73%) had 3D activation patterns across endocardial and epicardial layers.

Consequently, few studies have attempted to evaluate whether a combined endo‐epicardial ablation could result in better procedural outcomes after RF ablation. Some retrospective observational studies have analyzed the recurrence of VT in patients with ICM based on whether the ablation was performed via the endocardial or endo‐epicardial approach, with conflicting results [14, 15, 16, 17, 18, 19]. A recent meta‐analysis of six studies suggests an advantage of the endo‐epicardial approach over the endocardial approach (Relative risk reduction (RRR) = 0.43 [95% CI: 0.28–0.67]). No differences in terms of acute procedural success nor all‐cause mortality were observed, while a nonsignificant trend towards a higher risk of complication was noted (RRR = 1.88 [95% CI: 0.19–18.76]). [20] Bisceglia et al recently reported a low 3.6% risk of complications when epicardial ablation is performed in experienced centers [11]. More recently, Mohanty and al observed in a study of 361 patients with ICM VT that those receiving combined endo‐epicardial ablation had significantly lower 5‐year VT recurrence rates (45.6%) than those with only endocardial ablation (89.1%; *p* = 0.01) [26]. After adjustment, epicardial ablation significantly reduced VT recurrence risk (Hazard Ratio = 0.48; 95% CI = 0.27–0.86; *p* = 0.02). Although many studies have reported the safety and efficacy of a combined strategy in ICM patients, the level of evidence remains low, mainly based on retrospective observations with small patient populations, and no controlled, randomized study has confirmed this hypothesis. Notably, only one clinical trial (NCT02358746) has been registered since 2015 to evaluate this question, but was stopped due to inclusion issues.

The aim of the proposed multicentre, prospective, randomized trial is then to determine whether a first‐line combined endo‐epicardial ablation improves long‐term arrhythmia‐free survival in ICM patients compared to an endocardial‐only approach.

## Ethics Statement

The study has been approved by the National Ethics Committees (CPPs).

## Consent

All patients will give their written informed consent before taking part in the study. Each patient taking part in the study will also provide their written consent for access to their individual data for quality control purposes and the use of their data for the study analysis.

## Data Availability

The data that support the findings of this study are available from the corresponding author upon reasonable request.
